## 1.3 Research Aim, Objectives, and Outcomes

The study explores the possible interventions to improve patients’ therapeutic outcomes by medication adherence, structured diet, and exercise education. The research will investigate the impact of multifactorial interventions by pharmacists and clinical dietitian and electrolyte levels optimisation by physicians on the clinical outcomes in Emirati patients with type 2 diabetes.

The primary outcomes are as follows: (1) to evaluate the impact of pharmacist-led MTM on medications adherence, using a new pharmacist intervention protocol (MPIP), (2) to assess the effect of structure diet and exercise counseling with a specialized dietitian on anthropometry readings and carbohydrate as well as daily energy intake levels compared to control group, and (3) to assess the effect of the multi-factorial interventions on diabetic outcomes, including glycated haemoglobin A1c (HbA1c) level, blood pressure, and lipid profile.

The secondary outcomes are: (1) compare the effect of MPIP on regimen-specific medication possession ratio (MPR), and clinical interventions between both groups, (2) evaluate type, duration, and mean metabolic equivalent of task (METs) of physical activity per week during the follow up period between both groups, and (3) analyse serum electrolyte levels, cardiovascular risk factors, and eGFR levels in both group at study exit.

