## 2.2 Research Design

This is a randomised controlled, multidisciplinary trial. This research is a single-centre study, involving a 12-month follow-up period or till the date of participant withdrawal due to any cause, whichever comes first. The Study is not funded or supported by any grant or institute.

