## 2.3 Study Participants

The study will recruit Emirati patients previously diagnosed with T2DM from the endocrinology or chronic disease (CDC) clinics, who have will match the research inclusion criteria and have been taking the same diabetes medications for 12 weeks before the study with regular follow-up schedules in the previous year. Eligible patients will be randomized and blinded to the intervention and control groups.

The patients will be included in the analysis are those whose records are available in Salamtak (electronic medical record system operated by the Salamtak platform). At the end of the study, those with a medical history of cancer, chronic liver disease, high cardiovascular risk (defined as a 10-year predicted atherosclerotic cardiovascular disease (ASCVD) risk of ≥7.5% using the pooled cohort equation or a Framingham Risk Score of ≥20%), cardiac surgery within the last 12 months or any diabetic macrovascular complications will be excluded. Moreover, patients will be excluded either if they withdraw from the study or have a missed follow-up data including missed laboratory tests at the end of study period as per study protocol.

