Moreover, the control group will have their HbA1c levels recorded at least twice yearly (at initial and exit visits) in patients with stable glycaemic control meeting the treatment goals and quarterly in patients not meeting the treatment goals, which will be at the discretion of the attending physician [40]. Other laboratory tests will be performed twice yearly (or more frequently as per the physician’s request), and any major adverse cardiac events, emergency room visits or hospitalisations will be recorded and compared with baseline data.

The intervention group will receive multi-factorial interventions and assessments at initial visit and at each follow-up visit every 3 months after enrolment in the study. The multi-factorial interventions composed of the three below approaches: medication adherence counselling with medication therapy management program, diet and exercise counseling, and serum sodium, potassium and magnesium optimization (Figure 1).

- Adherence and MTM assessment.
- Diet and exercise assessment.
- Clinical outcomes and electrolyte level assessment.

Close-out

12-month visit

12-month visit

- Adherence counselling and MTM.
- Diet and exercise intervention.
- Multifactorial interventions with electrolytes level optimization.

Interventions

6-month visit

3-month visit

1-month visit

9-month visit

- Baseline laboratory tests, Na/K/Mg levels .
- Medication adherence questionnaire.
- Diet and exercise assessment.

Pre-assessment

Initial visit

Initial visit

Eligibility – Inclusion - Randomisation (1:1)

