Data verification will be performed on a weekly basis, and any missing data will be completed within 1 week of initial data collection and will be doubled-checked by two researchers before data analysis. Missing data in the final dataset will be filled by multiple imputation of the incomplete multivariate data using NORM® programme (version 2.03) integrated with SPSS, under a normal model and with two-level hierarchical linear modeling (HLM) analysis.

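### Randomised patients who withdraw or miss end-of-study data are dropped from the analysis, which can bias the comparison and conflicts with the planned multiple imputation for exit laboratory outcomes

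*Protocol*

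**What the plan says.** Section 2.3 gives the order of events. First, "Eligible patients will be randomized and blinded to the intervention and control groups". The next paragraph defines who enters the analysis and makes two kinds of removal.

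- **Withdrawal and missing data.** "patients will be excluded either if they withdraw from the study or have a missed follow-up data including missed laboratory tests" at the end of the study period.
- **Conditions applied at study end.** "At the end of the study, those with a medical history of cancer, chronic liver disease, high cardiovascular risk" (10-year ASCVD risk of 7.5% or more, or Framingham score of 20% or more), and "cardiac surgery within the last 12 months or any diabetic macrovascular complications will be excluded".

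Other sections bear on the same question:

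- Section 2.2 describes a design "involving a 12-month follow-up period or till the date of participant withdrawal due to any cause, whichever comes first", so data up to withdrawal are collected.
- Section 2.10 says "Missing data in the final dataset will be filled by multiple imputation of the incomplete multivariate data".
- Section 2.5 already lists high cardiovascular risk, recent cardiac surgery and macrovascular complications as exclusions, with the same cut-offs and the same 12-month window.
- Section 1.3 names HbA1c, blood pressure and lipid profile under the third primary outcome. A secondary outcome is to "analyse serum electrolyte levels, cardiovascular risk factors, and eGFR levels in both group at study exit".

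The protocol names no intention-to-treat or all-randomised analysis set.

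**The concern.** Randomisation makes the arms comparable only if the patients analysed are those allocated. Withdrawal and missed exit tests can only happen after allocation, so removing patients for them is post-randomisation selection on any reading of section 2.3.

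Losses may well differ by arm. Intervention patients have 3-monthly protocol visits, a pharmacist call within two weeks of each visit (section 2.8.1) and a monthly dietitian call (section 2.8.2). Controls receive usual care, with laboratory tests twice yearly or at the physician's request (section 2.8). If those who leave differ in prognosis, and do so at different rates in the two arms, the remaining groups differ even when the intervention does nothing. All three primary comparisons are exposed.

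Two further consequences follow.

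- The exclusion removes exactly the patients for whom imputation of exit laboratory values would be needed.
- It applies to the patient, not to the missing variable. The medication possession ratio (MPR), on which the first primary outcome is sized, comes from electronic refill records (section 2.8.1). A patient who misses only an exit blood test still has it observed, yet is dropped.

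**Working it through.** **1. The sections side by side.**

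| Question | Section 2.3 | Elsewhere in the protocol |
|---|---|---|
| Patient without exit laboratory tests | Excluded | Section 2.10: missing data imputed |
| Patient who withdraws | Excluded | Section 2.2: followed to the date of withdrawal |
| Cardiovascular risk, cardiac surgery, macrovascular disease | Applied at study end | Section 2.5: already excluded at entry |

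If everyone lacking exit laboratory tests is removed, no missing exit HbA1c or lipid value remains. For those outcomes the imputation has nothing to act on.

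On the third row, patients who met these criteria at entry should never have been randomised. A literal second application therefore removes mainly those who come to meet them later. With 12 months of follow-up, a 12-month look-back from study end is the follow-up year. ASCVD risk depends partly on blood pressure and lipids, which are primary outcomes.

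**2. The plan's own numbers.** Section 2.10 states 82 per group for MPR (difference 0.035, SD 0.09) and 84 for HbA1c (difference 0.5, SD 1.3), with 80% power and 5% alpha. With n = 2 × [(z_α + z_β) × SD / difference]² these reproduce at a one-sided 5% level: 81.8, rounded up to 82, and 83.6, rounded up to 84. (Sidedness is not stated; that is a separate matter.) Of 90 randomised per group, a 10% loss leaves 90 × 0.9 = 81, which is 1 below 82 and 3 below 84. The 10% allowance is for dropout only. It does not cover removals under the study-end criteria.

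**3. Size of a possible bias (assumed inputs).** Take no true effect on HbA1c, SD 1.3 (section 2.10), 90 per arm and a two-sided 5% test. Suppose a fraction q of an arm is removed and those removed lie s points above their arm's mean.

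- The mean of those kept falls by q × s / (1 − q).
- The spurious difference is the gap between the two arms' falls.
- SE = 1.3 × √(1/n₁ + 1/n₂), with n₁ and n₂ the numbers kept.
- Type I error = Φ(z − 1.96) + Φ(−z − 1.96), with z = difference / SE.

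The removal rates and shifts below are assumptions, not figures from the protocol.

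| Removed, one arm vs other | s | Falls | Spurious difference | SE | Type I error |
|---|---|---|---|---|---|
| 10% vs 10% | 1.0 | 0.111, 0.111 | 0 | 0.204 | 0.05 |
| 15% vs 5% | 0.5 | 0.088, 0.026 | 0.06 | 0.205 | 0.06 |
| 15% vs 5% | 1.0 | 0.176, 0.053 | 0.12 | 0.205 | 0.09 |
| 20% vs 10% | 1.0 | 0.250, 0.111 | 0.14 | 0.211 | 0.10 |
| 20% vs 5% | 1.0 | 0.250, 0.053 | 0.20 | 0.208 | 0.16 |

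The arm with the larger removal looks better, so the sign depends on which arm that is.

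**4. An extreme bound.** Suppose exactly the worst-controlled 10% leave one arm and a random 10% leave the other. The truncated-normal shift is φ(1.2816)/0.9 = 0.1755/0.9 = 0.195 SD, and 0.195 × 1.3 = 0.25 points, half the 0.5 target. A simulation of 20,000 trials (90 per arm, 9 removed from each, t-test) rejects in 27.2%. If the worst 5% leave instead, the shift is 0.14 points.

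**The case against.** Several points on the other side carry weight.

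- **The study-end list may be a drafting slip.** It nearly repeats section 2.5, a history of cancer is baseline language, and the assessments listed in section 2.8 include no exit ASCVD or Framingham calculation. A reader might infer that the protocol plainly removes patients for events and risk levels arising after allocation. That is the literal reading, but not the only one. What stands is that the timing words are wrong or harmful and must be reconciled with section 2.5.
- **Cardiac events are not a listed outcome.** A reader might infer that patients are removed for an outcome event. Section 2.8 does say "any major adverse cardiac events, emergency room visits or hospitalisations will be recorded and compared with baseline data", but in its account of the control group, and section 1.3 lists no such outcome. Only the overlap with blood pressure and lipids is supported.
- **The clash with imputation is not total.** The final dataset could mean what is left after exclusions, with imputation for questionnaires, interim visits or baseline items. The protocol does not say so, and the conflict remains for exit laboratory outcomes.
- **The difference in contact has limits.** Controls also see a physician every 3 months and get a reminder call, and exit assessments are planned in both arms. Losses may differ; nothing shows that they will.
- **Consent can be withdrawn** (section 2.9), so analysing everyone cannot mean using data collected after that.

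None of this touches the exclusion for withdrawal and missing data, which is post-randomisation however it is read.

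**Conclusion.** The point holds, resting on the exclusion of randomised patients who withdraw or miss follow-up data. It can bias all three primary comparisons, can discard observed MPR, and conflicts with section 2.10 for exit laboratory outcomes. It must be fixed: this is a rule the protocol states, not a detail left to an analysis plan. The study-end risk list is a second, ambiguous defect of wording.

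It would go too far to say that the trial will be biased, or biased towards benefit. Losing more poorly controlled patients from the control arm would tend to hide a benefit; losing more from the intervention arm would create a false one. The documents settle neither direction nor size. On the assumed inputs, the spurious HbA1c difference is about 0.06 to 0.20 points with type I error 0.06 to 0.16, against a target of 0.5. The 0.25 points and 27% are an extreme bound, and equal removal with an equal shift gives no bias.

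**What to change.** In section 2.3:

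- Delete the exclusion for withdrawal and missing follow-up data.
- Delete the words that apply eligibility criteria at study end, and reconcile the list with section 2.5.
- State that eligibility is judged only on data from before allocation.
- State that all randomised participants are analysed in their assigned group, using data collected up to any withdrawal of consent.

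In section 2.10, state that missing exit values are handled by the multiple imputation already planned, with the baseline value of the outcome included in the model, and that the completers-only analysis is a sensitivity analysis.

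The cost is protocol wording and a little more analysis. No new data are needed.

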## 2.4 Inclusion Criteria

- Male or female Emirati patients between 30 and 65 years of age.
- The patient has been previously diagnosed with type 2 diabetes mellitus recorded in Salamtak, defined in our diagnostic criteria.
- Previously on diabetic medication recorded in Salamtak and antihyperglycemic therapy must be unchanged for 12 weeks before the study.
- Patients with normal or mildly/moderately abnormal serum magnesium and/or potassium levels.
- Patients with normal to moderately impaired renal function, defined as an estimated glomerular filtration rate (eGFR) of >30 mL/min/1.73 m2, for more than 3 months at baseline (stages G1, G2, G3a and G3b of chronic kidney disease) [39].
- Body Mass index less than 40 at study enrollment.

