## 1.4 Hypothesis and Significance of The Research

In this research, we hypothesise that adherence to medication and exercise, in type 2 diabetic patients, will lead to improvement in patients’ clinical outcomes. The interventions in this research will offer recommendations for healthcare providers to adopt reliable measurable factors to improve diabetic outcomes, which eventually will lessen the burden of diabetes, medication cost in UAE and improve patient satisfaction by reducing or delaying macrovascular complications from diabetes.

In this study medication adherence will be measured by a validated Arabic version of medication adherence questionnaire, which is new in our region and in UAE. The revised Summary of Diabetes Self-Care Activities measure (SDSCA) scale will be used to evaluate adherence to diet and exercise was validated numerically. Moreover, the effects of different serum electrolytes levels including serum sodium, potassium, and magnesium levels on kidney function during the diabetes course will be investigated in this research.

The expected outcomes of the research are summarized as follow:

- Improve medication adherence measured by fixed medication possession ratio (MPR) equation and a validated questionnaire with the new pharmacy intervention protocol in the intervention compared to the control group.
- Achieve better exercise and diet adherence with overall reduction in total carbohydrate and energy intake in the intervention compared to the control group.
- Increase the number of patients reaching the target HbA1c level of < 7% and blood pressure target of 130/80 after one year in the intervention compared to the control group.
- Improved serum electrolyte levels (including serum Na, K, and Mg) in the intervention compared to the control group.
- Reduction in cardiovascular risk factors (such as wight and BMI) and improvement in eGFR levels in the intervention compared to the control group, within the study observation period.

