## 2.5 Exclusion Criteria

- Non-Emirati patients or patients without full insurance coverage.
- Patients with severe or symptomatic hypo- or hypermagnesemia and/or hypo- or hyperkalaemia, metabolic acidosis or hypophosphatemia with or without proximal renal tubular acidosis and Fanconi syndrome.
- Patients with prolonged hypokalaemia with surreptitious diuretic use, laxative abuse, eating disorders or primary aldosteronism.
- Patients receiving medications that may cause drug-induced acute renal failure during the observational period and may be implicated in hypomagnesaemia (e.g. aminoglycoside antibiotics, cyclosporine, amphotericin B, cisplatin, pentamidine and foscarnet).
- Patients who have undergone bariatric surgery within the past two years or other gastrointestinal surgeries that induce chronic malabsorption.
- Pre-menopausal women who are nursing or were pregnant within the last 12 months.
- Blood dyscrasias or any disorders causing haemolysis or unstable red blood cell population (e.g., malaria, babesiosis, haemolytic anaemia).
- Stage 4 or 5 CKD patients, with a severe reduction in glomerular filtration rate, kidney failure or dialysis, defined as GFR ≤ 29 ml/min or albumin/creatinine ratio ˃ 30 mg/mmol as baseline value.
- High cardiovascular risk, defined as 10-year predicted atherosclerotic cardiovascular disease (ASCVD) risk ≥7.5% by Pooled Cohort Equation or Framingham risk score ≥20%, or cardiac surgery, or angioplasty within the last 12 months or any diabetic macrovascular complications as defined in our definition.
- Indication of liver disease, defined by serum levels of either alanine aminotransferase (ALT), aspartate aminotransferase (AST) or alkaline phosphatase (ALP) above 3 x upper limit of normal as defined at the beginning of the study or within the last 12 months.
- Medical history of cancer and/or treatment for cancer within the last five years, or immune compromised patients.
- Treatment with systemic steroids or change in dosage of thyroid hormones within the last 12 months after starting the study or any other uncontrolled endocrine disorder.
- Patient with communication barriers that may affect obtaining patient adherence, receiving diet, exercise counselling or consent signing, and include:
- a. Patients with severe emotional distress.
- b. Patients who are unable to use mobile applications or access the internet for any reason.

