### 2.8.3 Electrolyte Optimization Including Serum Sodium, Potassium as well as Magnesium Levels

During the follow-up, the intervention group will be evaluated for electrolyte imbalance, particularly Na, K, and Mg levels. The metabolic panel (including serum Na, K, and Mg levels) and eGFR will be measured at baseline and at 3, 6, 9 and 12 months after recruitment. Moreover, participants will be evaluated for symptoms of electrolyte imbalance. In patients with no or minimal symptoms of mild to moderate hyper-, hypo-, or hypernatremia [61, 62] hypomagnesaemia [63] and/or hyper- or hypokalaemia [64, 65], treatment is initiated based on the recommended clinical pathway with the primary goal of preventing or treating life-threatening complications while diagnosing and treating the underlying disease [66-68].

At the end of the trial, we will assess the effect of serum electrolyte level optimization during medical investigation on diabetes management, clinical outcomes, as well as kidney function measured by estimated glomerular filtration rate (eGFR) levels.

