## 2.10 Statistical Analysis

The sample size required to reach significant in the three primary outcomes in the study’s multi-intervention approach is 180 participant (90 participants in each group). Sample size was calculated with Giga sample size online calculator [69], according to a pilot analysis of 50 participants matching study protocol, with a power of 80% with alpha level of 5% to detect the minimal difference of each primary outcomes in the study.

For 1^st^ outcome, the baseline medication possession ratio (MPR) for those 50 participants was 0.93 ± 0.09 (mean ± SD), we determined that a target of 82 participants per group would be required for a minimum detectable effect of 0.035 between both groups. A total sample size of 180 was calculated, assuming dropout rate of 10% in both groups.

For 2^nd^ outcome, the mean body mass index (BMI) (mean ± SD) of the 50 participants was 31.2 ± 6.4, and the total number of participants required to detect minimum detectable difference of 2.5 in BMI between groups was 180 participants, powered for 80% with α equal to 0.05, considering drop rate of 10% throughout the study period.

In addition, for 3^rd^ outcome to detect minimal difference of 0.5% in HbA1c between groups with mean HbA1c = 7.7 ± 1.3 (mean ± SD) at baseline (for the same 50 participants), a total sample size of 184 participants were calculated with 84 participants per group were required, considering 10% expected dropout rate during the follow-up period.

For data analysis, the difference between both groups will be tested for normality using the Shapiro–Wilk test. Data will be presented as percentages for categorical variables or mean ± SD or median (25th, 75th percentiles) for continuous variables. Chi-square test will be used for the categorical variables, whereas student’s t-test will be used for normally distributed continuous variables, or Mann–Whitney U test for non-normally distributed continuous variables.

Analyses will be performed using IBM SPSS Statistics (version 26), and differences will be considered significant for a p-value of <0.05.

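### The electrolyte outcome is stated as serum levels at exit although potassium and sodium are corrected in both directions, so a difference in mean level is not clearly an improvement and may miss a real correction

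*Protocol*

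**What the plan says.** **Who enters.** Protocol section 2.4 admits "Patients with normal or mildly/moderately abnormal serum magnesium and/or potassium levels" and names no direction. Section 2.5 removes "Patients with severe or symptomatic hypo- or hypermagnesemia and/or hypo- or hyperkalaemia". Read together, mild or moderate low values, normal values and mild or moderate high values of potassium and magnesium all qualify. Section 2.4 sets no sodium criterion.

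**What the intervention does.** Section 2.8.3 covers disorders of sodium on both sides (its wording there is garbled but includes hypo- and hyper- states) and continues: "hypomagnesaemia [63] and/or hyper- or hypokalaemia [64, 65], treatment is initiated based on the recommended clinical pathway". Potassium is therefore corrected upwards and downwards. For magnesium, only the low state is named.

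**What is measured as success.** Secondary outcome 3 in section 1.3 is to "analyse serum electrolyte levels, cardiovascular risk factors, and eGFR levels in both group at study exit". The matching expected outcome in section 1.4 is "Improved serum electrolyte levels (including serum Na, K, and Mg) in the intervention compared to the control group". Neither gives a direction, a reference range or a subgroup of patients abnormal at baseline.

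**How it is tested.** Section 2.10 has one general rule: chi-square for categorical variables and, for continuous ones, Student's t ("test will be used for normally distributed continuous variables, or Mann–Whitney U test for non-normally distributed continuous variables").

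**A contrast within the protocol.** For HbA1c, section 1.4 uses target attainment: "Increase the number of patients reaching the target HbA1c level of < 7" percent. Blood pressure is treated the same way. Electrolytes are not.

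**The concern.** Potassium, sodium and magnesium have a normal range with two limits. A higher mean is not better in itself, and nor is a lower one. If an arm contains both low and high values and both are brought into range, the low group pulls the arm mean up, the high group pulls it down, and patients who were normal throughout do not move it. The contrast in means is then the net of two opposing shifts, diluted by the normal patients.

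Two misreadings follow. A real correction may leave little or no difference in means and be reported as no effect on electrolytes. A significant shift in the mean may be reported as improvement although it could equally reflect values pushed too far one way. Electrolyte optimisation is one of the three components of the intervention (section 2.8), so the outcome that shows whether this component worked should be able to show it.

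**Working it through.** **The plan's own figure.** There is none for electrolytes: section 2.10 gives no effect size, SD or sample size for them. From section 2.10 I take only the arm sizes, 90 per group planned and 82 per group required for the medication possession ratio.

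**Assumed inputs (potassium, illustration only).** The documents give no reference range, SD, baseline mix or correction rate. I assume:
- a range of 3.5 to 5.1 mmol/L;
- normal and corrected values with mean 4.3 and SD 0.3;
- low values with mean 3.2 and high values with mean 5.4, each with SD 0.12;
- 80% of abnormal patients corrected in the intervention arm, and initially none in the control arm;
- two-sided alpha of 0.05.

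**Step 1: difference in means.** With f_low and f_high the baseline shares:

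D = 0.8 × [f_low × (4.3 − 3.2) − f_high × (5.4 − 4.3)] = 0.88 × (f_low − f_high)

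- 10% low, 10% high: 0.88 × 0 = 0
- 15% low, 5% high: 0.88 × 0.10 = 0.088
- 20% low, none high: 0.88 × 0.20 = 0.176

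**Step 2: share in range.** A normal or corrected value is in range with probability P(|z| < 0.8/0.3) = 0.992. An uncorrected abnormal value is in range with probability P(z > 0.3/0.12) = 0.006. With 20% abnormal:

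- intervention: 0.992 × (0.80 + 0.16) + 0.006 × 0.04 = 0.95
- control: 0.992 × 0.80 + 0.006 × 0.20 = 0.80

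This share is the same whether the 20% are low, high or mixed.

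**Step 3: simulated power, 90 per arm.**

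| Low / high at baseline | D | t-test | Mann–Whitney | Chi-square, in range |
|---|---|---|---|---|
| 10% / 10% | 0.00 | 5% | 5% | 92% |
| 15% / 5% | 0.09 | 24% | 15% | 92% |
| 5% / 5% | 0.00 | 5% | 5% | 57–58% |
| 20% / 0% | 0.18 | 74% | 46% | 91–92% |

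The 5% entries are simply the type I error rate. The last row has no cancellation; what remains is dilution by the 80% who were normal. At 82 per arm, chi-square power for the 10/10 mix is about 89%.

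**Step 4: relax the control assumption.** If 30% of abnormal controls normalise, the control share in range for the 10/10 mix is 0.992 × (0.80 + 0.06) + 0.006 × 0.14 = 0.85. At 50% it is 0.992 × (0.80 + 0.10) + 0.006 × 0.10 = 0.89. At 90 per arm, chi-square power falls from 92% to about 64% and 31%. For the 5/5 mix it falls from about 58% to 28% and 15%. The difference in means stays at zero in both mixes.

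**Step 5: a second set of assumptions.** With a range of 3.5 to 5.0, milder abnormal values (3.0 to 3.5 and 5.0 to 5.5), full correction, no normalisation in controls and 82 per arm, the pattern is the same:
- balanced mixes: t-test 5%, chi-square 97 to 100%;
- 15% low, 10% high: t-test 11%, chi-square 100%;
- 15% low, 5% high: t-test 32%, chi-square 100%;
- 15% low, none high: t-test 71%, chi-square 99.9%.

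**The case against.** **The analysis is partly inferred.** Section 1.3 says only that levels will be analysed, section 2.10 is a general rule, and an improved level could be read as a normalised one. A statistical analysis plan that is not shown could add in-range coding. This has some force. But the outcome the protocol states is the level, its rule for continuous variables is a comparison of location, and section 1.4 uses target attainment for HbA1c and blood pressure and not here. A later in-range analysis would be an addition to the stated outcome.

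**The rationale is one-directional.** Section 1.2 speaks of treating low sodium, low potassium and low magnesium. If low values predominate, a higher mean is the expected direction, and the loss is dilution. This stands, above all for magnesium, where section 2.8.3 names only the low state. A reader might infer that cancellation applies equally to all three electrolytes; for magnesium the text does not support that.

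**A reader might also infer that the outcome cannot detect an effect.** That goes too far. With 20% low and none high, the t-test has 74% power in the illustration. A zero difference needs balanced shares and balanced shifts, and the baseline mix is unknown.

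**The power figures favour the remedy.** This stands. Controls see their physician every 3 months and have other laboratory tests at least twice yearly (section 2.8), so some will be corrected or will normalise unaided. The 92% is a best case, and 90 per arm is the number before dropout. The in-range proportion may itself be underpowered, though it had the higher power in every scenario listed.

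**The consequence is limited.** Section 2.8.3 judges optimisation by diabetes management, clinical outcomes and eGFR as well. A null difference in mean electrolytes therefore need not be read as failure of the component.

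**Conclusion.** The concern holds in a limited form. For potassium the entry criteria admit both directions and the intervention corrects both; for sodium the intervention corrects both. For these two, a difference in mean level at exit has no clear meaning as improvement and may fail to show a real correction. The loss ranges from complete (balanced mix), through partial (unequal mix), to dilution only (one direction). For magnesium it is mainly dilution.

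The size cannot be fixed from the documents. In the illustration with 10% low and 10% high, power is 5% for the t-test against about 92% for the in-range proportion at best, and about 64% or 31% if 30% or 50% of abnormal controls normalise. These figures rest on the assumed range, SDs, mix and correction rates.

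The outcome is secondary and carries no power claim. The three primary outcomes and the sample size are untouched. The inclusion criterion itself is not at fault; the outcome wording does not fit the population and the two-way treatment. The change is worth making because it costs very little.

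**What to change.** In sections 1.3 and 1.4, define the electrolyte outcome separately for sodium, potassium and magnesium as the proportion of patients within the central laboratory's reference range at month 12. Compare arms with the chi-square test already planned in section 2.10. Also report the proportion normalised among patients abnormal at baseline. Report mean levels alongside, and state that a higher or lower mean is not in itself taken as improvement.

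The cost is one derived variable per electrolyte, from panels already scheduled at baseline and exit, plus the wording change. No new measurement is needed. The downside is some loss of information from dichotomising, which reporting the levels alongside partly offsets. Because the in-range comparison may also have modest power if controls normalise, it should be reported with a confidence interval for the difference in proportions.
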